## **7.9 Patients parameters to recorded in the CRF**

### **7.9.1 Visit 1: Screening and enrolment**

- Pregnancy test
- Patients date of birth, gender, height and weight
- Medical history and type of admission
- Concomitant therapy
- Infection site, type of infection and documented microbial agents
- Antibiotic therapy
- Inclusion and exclusion criteria
- Baseline blood sample: PCT, Lactate, pH
- Endotoxin activity (EAA) measurement
- SAPS score
- Hemodynamic parameters
- Catecholamine doses

### **7.9.2 Visit 2: Treatment start**

- Randomization to either SOC treatment, or SOC with oXiris™ hemofiltration, or SOC with Toraymyxin™ hemoperfusion
- EAA measurement
- IL-6 and HMGB1 measurement
- Catheter implementation
- Hemodynamic parameters: MAP, CVP, HR, CO, ELWI, PVPI
- Catecholamine doses: Epinephrine, norepinephrine, dobutamine dose
- Volume requirement
- Ventilation parameters: SaO2, FiO2, SvO2
- Urine output (ml/d)
- SOFA score, SAPS II ScorePCT, Lactate, pH

### **7.9.3 Visit 3 (24 hours) and Visit 4 (48 hours): Treatment period**

- EAA measurement
- IL-6 and HMGB1
- PCT, Lactate, pH
- SOFA score
- Catecholamine doses: Epinephrine, norepinephrine, dobutamine dose
- Volume requirement
- Hemodynamic parameters: MAP, CVP, HR, CO, ELWI, PVPI
- Ventilation parameters: SaO2, FiO2, SvO2
- Urine output (ml/d)
- AE/SAE
- In the SOC with oXiris™ treatment and SOC with Toraymyxin™ treatment groups:
  - Date and time of initiation and termination of each treatment, anticoagulation usage
  - Documentation of achievement of the treatment period or reason for premature disconnection.
- In the SOC treatment group:
  - If renal replacement therapy has to be performed: type of RRT, type of membrane, treatment conditions, duration, and anticoagulation.

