### **6.4 Secondary endpoints**

The secondary endpoints are the following:

- Measurement of IL-6 and HMGB1 T0 i.e. patient inclusion, at T24 hours, T48 hours, and T 72 hours after treatment initiation;
- Routine measurements of norepinephrine dose, inotropic score, and vasopressor dependency index T0, T24, T48 and T72;
- Haemodynamics: MAP, CVP, HR, CO, ELWI, PVPI T0, T24, T48 and T72
- Routine measurements of volume requirement T0, T24, T48 and T72;
- Routine measurements of ventilation parameters PO2/FiO2, SvO2 T0, T24, T48 and T72;
- Urine output (ml/d)
- Lactate, procalcitonin and pH measurements at T0, T24, T48 and T72 after treatment initiation;
- SOFA score calculation at T0, T24, T48 and T72 ;
- Incidence of renal failure, ICU length of stay
- Patient survival at D28;
- Recording of AEs/SAEs

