### **7.4 Study population**

#### **7.4.1 Inclusion Criteria**

The following inclusion criteria should be fulfilled at the time of enrollment within 24h of suspected septic shock.

Patients with septic shock, defined as: persistent catecholamine dependency with a vasopressor index > 3 after fluid resuscitation with at least 30ml/kg of i.v. fluid administered

prior to time of randomization, and at least ONE of the following criteria: metabolic acidosis, neurologic dysfunction (GCS  $\leq 14$ ), renal dysfunction, (RIFLE Class Injury or Failure), or hepatic dysfunction (Transaminases  $\geq$  twice upper limit of normal).

- Male and Female patients  $\geq 18$  years
- Endotoxin levels  $\geq 0.6$  IU within 24h from the time of suspected septic shock. If the first Endotoxin level is  $\geq 0.4 \leq 0.6$  IU EAA, the measurement should be repeated 2-3 times within the screening period of 24 hours.

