### **7.6.1 Concomitant medication**

Any medication or treatment required for the welfare and health of the patients enrolled in the study will be administered at the investigator's discretion. All such concomitant medications shall be reported on the CRF during the patient's stay in ICU i.e. from the signature of the discharge from ICU.

Vasopressin and corticosteroids for the treatment of septic shock are not allowed in the study. In patients without pre-existing chronic corticosteroid treatment, corticosteroids are not allowed in the study.

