#### Treatment parameters

Mode: CVVHDF: 20% diffusion-80% convection

Dose: 35 ml/h/kg\*

Reinfusion: 50% Predilution, 50% Postdilution

Blood flow rate (Qb): 150 ml/min at least.

Filtration Fraction should be inferior to 15%.

Once hemodynamic stabilization is achieved, fluid overload should be managed according to the patient clinical needs.

\*prescribed dose to secure a delivered dose of min 25ml/h/kg

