### **7.6.5 Occurrence of acute renal failure during study period**

#### **Initiation of Renal Replacement Therapy**

Patients with acute renal failure requiring renal replacement therapy will be treated with continuous renal replacement therapy irrespective of their randomization group. Criteria to start CRRT are the following:

- Metabolic acidosis with a pH<7.2
- HCO3 <16mmol/l
- Urine- output <20ml/h
- Uncontrolled hyperkalaemia
- Fluid overload

The oXiris™ product cannot be used in the Standard of Care group nor and Toraymyxin™ treatment group. The hemofiltration in these groups will be performed with the MultiFiltrate™ (Fresenius) and the AV1000S haemofilter or the Prismaflex®-system and the Prismaflex ST150 haemofilter according to our SOP.

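### RRT details are listed for the SOC arm only; separately, the assigned CVVHDF shifts creatinine-scored SOFA and pH at T24 and T48 towards oXiris relative to comparators not on CRRT

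*Protocol*

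**What the plan says.** - **Recording.** In section 7.9.3 (24 and 48 hours), under "In the SOC treatment group", the CRF list asks for "If renal replacement therapy has to be performed: type of RRT, type of membrane, treatment conditions, duration, and anticoagulation". For the two device arms it asks for "Date and time of initiation and termination of each treatment, anticoagulation usage", plus completion of the treatment period or the reason for stopping early. It has no CRRT line for those arms. Section 7.9.4 (72 hours) has no RRT line for any arm.
- **CRRT in every arm.** Section 7.6.5 states: "Patients with acute renal failure requiring renal replacement therapy will be treated with continuous renal replacement therapy irrespective of their randomization group". Section 7.6.4 describes CRRT in Toraymyxin patients and names two permitted haemofilters. Section 7.6.3 moves oXiris patients who still need RRT after 48 hours to the usual CRRT set.
- **The oXiris treatment.** Section 7.6.3 sets 48 hours, "Mode: CVVHDF: 20% diffusion-80% convection", with 35 ml/h/kg prescribed to secure at least 25 ml/h/kg delivered. Section 7.2.1 names bicarbonate fluids. Section 5.1.3 accepts that some patients will be treated without needing RRT, and estimates that about 50% of patients with severe sepsis eventually need it.
- **Endpoints.** Section 6.4 lists SOFA and pH at T0, T24, T48 and T72, and "Incidence of renal failure, ICU length of stay", without defining renal failure. The SOFA table in section 7.8.3.2 scores the renal item on creatinine only. In section 7.4.1, "renal dysfunction, (RIFLE Class Injury or Failure" is one of four alternative qualifying dysfunctions.
- **Oxygenation.** Section 6.4 and the SOFA table need PaO2, but the visit lists in sections 7.9.2 to 7.9.4 name SaO2, FiO2 and SvO2.

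**The concern.** There are two separate problems.

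The first is an inconsistency about data. The protocol provides for CRRT in all three arms but asks for its details in one. Section 13 plans to adjust for factors that differ between groups, and RRT exposure is an obvious candidate. An analysis plan cannot recover details that the CRF never requested. The membrane also matters for IL-6 and HMGB1, because section 5.1 attributes their adsorption to the membrane type.

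The second concerns what two secondary endpoints measure. CVVHDF clears creatinine and bicarbonate fluid corrects pH. All oXiris patients have this running, or just ending, at T24 and T48; comparators have it only when RRT is indicated. A lower SOFA or better pH in the oXiris arm at those times could come from the circuit alone. The pilot is meant to supply data for designing later studies, so such a difference could be carried into their planning.

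**Working it through.** The protocol gives no calculation for these endpoints, so there is no figure to reproduce. Its 10 analysed patients per group (section 7.7) agree with 30 in total (section 13).

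**1. Recording, side by side**

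| Arm | CRRT foreseen | RRT details, 7.9.3 | RRT details, 7.9.4 |
|---|---|---|---|
| SOC | 7.6.5 | yes | none |
| Toraymyxin | 7.6.4, 7.6.5 | none | none |
| oXiris after 48 h | 7.6.3 | none | none |

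**2. Creatinine washout.** Clearance K is 25 or 35 ml/h/kg (section 7.6.3). The distribution volume V is assumed to be 0.5 to 0.7 L/kg. With no generation, the fraction left is exp(−Kt/V).
- 24 h: exp(−0.035×24/0.5) = 0.19 to exp(−0.025×24/0.7) = 0.42
- 48 h: 0.03 to 0.18

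**3. Renal SOFA points.** Assumed, not in the protocol: V = 0.6 L/kg, starting creatinine C0 = 350 µmol/l, generation g = 3.7 to 7.4 µmol/kg/h, residual renal clearance kr = 0 to 20 ml/h/kg. With k = K + kr in L/h/kg,

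C(t) = g/k + (C0 − g/k)·exp(−kt/V).

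Example with g = 5.5, kr = 10:
- No RRT, 24 h: 550 − 200×exp(−0.4) = 416, 3 points
- K = 35, 24 h: 122.2 + 227.8×exp(−1.8) = 160, 1 point

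| g | kr | K | 24 h: no RRT / CVVHDF (points) | 48 h: no RRT / CVVHDF (points) | Gap, 24 h / 48 h |
|---|---|---|---|---|---|
| 5.5 | 10 | 35 | 416 (3) / 160 (1) | 460 (4) / 128 (1) | 2 / 3 |
| 3.7 | 20 | 25 | 259 (2) / 126 (1) | 218 (2) / 90 (0) | 1 / 2 |
| 7.4 | 20 | 25 | 361 (3) / 195 (2) | 366 (3) / 170 (2) | 1 / 1 |

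Over the whole grid the gap is 1 to 3 points. At kr = 20 it is 1 to 2.

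**4. Arm level.** The gap exists only against comparators not on CRRT. If 50% of comparators receive RRT, the mean shift among patients like the modelled one is 0.5×1 = 0.5 to 0.5×3 = 1.5 points. The 50% refers to eventual need, so fewer may be on RRT at T24 or T48 and the dilution may be smaller. Conversely, a patient whose creatinine would stay below 106 µmol/l without RRT scores 0 either way and contributes nothing.

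**5. T72.** The oXiris course ended 24 hours earlier, so its effect there is carry-over only.

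**6. Incidence of renal failure.** Take 10 patients per arm, 5 SOC cases (the 50% figure) and a two-sided Fisher's exact test.
- Every oXiris patient counted because on CVVHDF, 10/10 vs 5/10: p = 2×C(10,5)/C(20,5) = 2×252/15504 = 0.033, against oXiris
- No oXiris patient counted because already on CVVHDF, 0/10 vs 5/10: p = 0.033, in favour of oXiris
- Only renal indications counted, 5/10 vs 5/10: p = 1.0

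**7. pH.** Only the direction follows from the documents. No size was derived.

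**The case against.** **RRT outside SOC may not be lost.** The flow chart in section 3 requires concomitant therapy at every visit in all arms, and section 7.6.1 speaks of "Any medication or treatment required for the welfare and health of the patients enrolled in the study will be administered at the investigator's discretion". The section 7.9 lists are also incomplete elsewhere: section 7.9.4 omits volume requirement, which the flow chart asks for at that visit. The comparator haemofilters are limited to two named types. This stands in part. The fact of RRT may be captured, so a reader should not infer that CRRT outside SOC goes unrecorded. But the type, membrane, conditions and duration are requested for SOC alone.

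**Renal support is part of what oXiris offers.** Section 5.1 presents the device as covering renal support, so better pH and creatinine are partly its effect. That is a fair account of total benefit. It does not make a lower creatinine score evidence of organ recovery or of endotoxin removal.

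**The sickest patients are cleared in every arm.** A reader might model an anuric patient with creatinine of 450 µmol/l and claim 2 to 3 points for oXiris. With no residual function that patient would probably meet the urine-output criterion in section 7.6.5 and receive CRRT whatever the arm. The within-patient fall is real, but it is not a between-arm effect. The contrast comes from patients with residual function, hence the grid above.

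**Endpoint definitions can sit in the analysis plan.** The definition of renal failure can, and its absence here is not the finding. The SOC-only CRF fields and the creatinine-only SOFA table are fixed in the protocol.

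**Conclusion.** The point holds in two limited parts. First, section 7.9.3 (SOC-only RRT details) and section 7.9.4 (none) do not fit sections 7.6.3 to 7.6.5, and must be reconciled. Second, total SOFA and pH at T24 and T48 are shifted towards oXiris relative to comparators not on CRRT, regardless of kidney recovery or endotoxin effect. For SOFA the shift is about 1 to 3 renal points against a patient on no RRT, and roughly half that at arm level with 50% RRT among comparators. This rests on the assumed creatinine kinetics and a raised starting creatinine.

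Three stronger readings are not supported:
- A reader might infer that the recording gap causes the shift. The assigned CVVHDF causes it and would do so with perfect records; the gap only hampers describing or adjusting for it.
- A reader might infer that incidence of renal failure favours oXiris by design. It is undefined and can go either way. Nothing in the protocol says that renal dysfunction present at entry will be counted as new.
- A reader might extend the point to the main result. The primary endpoint is endotoxin activity at 72 hours; only secondary endpoints are affected.

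The change should be made, but the trial's primary conclusion does not depend on it.

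**What to change.** - Extend the RRT fields to all three arms at Visits 3 to 5: yes/no, indication, start and stop, type, membrane and dose. Record RRT status to day 28. Reconcile sections 7.9.3 and 7.9.4 with sections 7.6.3 to 7.6.5.
- Report SOFA without the renal item alongside total SOFA, in every arm.
- Count renal failure by a renal indication independent of the assigned CVVHDF, and separate cases present at Visit 2 from new ones.
- Treat pH at T24 and T48 as descriptive in comparisons with oXiris.
- List PaO2 with the ventilation parameters, to match section 6.4 and the SOFA table. This looks like a listing slip.

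Do not carry forward the pre-RRT renal score. That would freeze the item in every oXiris patient while untreated comparators could still improve, and so introduce a new bias.

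The cost is a few CRF lines, some endpoint wording and one extra SOFA analysis. Study treatment does not change.

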#### 7.9.4 Visit 5: Follow-up 72 hours after treatment initiation

- EAA measurement
- Signed and dated informed consent of relatives and independent doctor (see p. 30).
- IL-6 and HMGB1
- PCT, Lactate, pH
- SOFA score
- Catecholamine doses: Epinephrine, norepinephrine, dobutamine dose
- Hemodynamic parameters: MAP, CVP, HR, CO, ELWI, PVPI
- Ventilation: SaO2, FiO2, SvO2
- Urine output (ml/d)
- AE/SAE
- Informed consent

#### 7.9.5 Visit 6: Outcome

- Discharge from ICU
- Discharge from hospital
- Survival 28 days  $\pm$  7 days after randomization. Patients will be contacted by phone, if the patient is no longer in hospital. In case, documented attempts to contact the patient have failed, a rapid contact with the patient's general practitioner will be initiated. To be in line with the data protection requirements the patients gives the consent to contact the general practitioner in the informed consent form. Date of death (if applicable)
- AE/SAE

#### 7.9.6 Study termination

When a patient completes the study, the study termination form has to be completed.

## 8 Adverse events and adverse device effects

### 8.1 Definitions

**Adverse Device Effect:** Adverse event related to the use of an investigational medical device. This includes any AE resulting from insufficiencies or inadequacies in the instructions for use, the deployment, the implantation, the installation, the operation, or any malfunction of the investigational medical device. This includes any event that is a result of a use error or intentional misuse.

**Adverse Events:** Any untoward medical occurrence, unintended disease or injury or any untoward clinical signs (including an abnormal laboratory finding) in subjects, users or other persons whether or not related to the investigational medical device. This includes events related to the investigational device or the comparator and to the procedures involved (any procedure in the clinical investigational plan. For users or other persons this is restricted to events related to the investigational medical device.

**Device Deficiency:** Inadequacy of a medical device with respect to its identity, quality, durability, reliability, safety or performance, including malfunctions, use errors, and inadequate labelling.

**Serious Adverse Device Effect:** Adverse device effect that has resulted in any of the consequences characteristic of a serious adverse event.

**Serious Adverse Event:** Adverse event that

- led to a death,
- led to a serious deterioration in health of subject, that either resulted in
  - 1) a life-threatening illness or injury, or
  - 2) a permanent impairment of a body structure or a body function, or
  - 3) in-patient or prolonged hospitalisation, or
  - 4) medical or surgical intervention to prevent life-threatening illness or injury or permanent impairment to a body structure or a body function,
- led to foetal distress, foetal death or a congenital abnormality or birth defect.

This includes device deficiencies that might have led to a SAE if

- suitable action had not been taken or
- intervention had not been made or
- if circumstances had been less fortunate.

These are handled under the SAE reporting system. A planned hospitalization for pre-existing condition, or a procedure required by the Clinical Investigation Plan, without serious deterioration in health, is not considered to be an SAE.

A **Serious Deterioration** in state of health includes:

- a) life-threatening illness,
- b) permanent impairment of a body function or permanent damage to a body structure,
- c) a condition necessitating medical or surgical intervention to prevent a) or b) (e.g. clinically relevant increase in the duration of a surgical procedure or a condition that requires hospitalisation or significant prolongation of existing hospitalisation)
- d) any indirect harm as a consequence of an incorrect diagnostic or in vitro diagnostic test results when used within manufacturer's instructions for use,
- e) foetal distress, foetal death or any congenital abnormality or birth defects.

**Unanticipated Serious Adverse Device Effect:** Serious adverse device effect that by its nature, incidence, severity or outcome has not been identified in the current version of the risk analyses report.

If there is any doubt about whether or not an AE has to be considered serious, the Principle Investigator should be contacted.

## **8.2 Foreseeable Adverse Events and Adverse Events related to Clinical Outcomes**

All Adverse Events (AE) will be collected during study days 0 to 28 (or until death).

The following events will be considered as clinical outcomes:

- Death related to septic shock, that is, related to septic shock or a sequel of sepsis based on the interpretation of the investigator
- Cardiovascular events: the need for vasoactive drugs or hypotension.
- Respiratory events: decreased PaO2/FiO2 mechanical ventilation, hypoxia, acute respiratory distress syndrome, acute lung injury or respiratory failure
- Hepatic events: hepatic injury or liver dysfunction that leads to an increase from baseline in the serum level of bilirubin
- Hematologic/coagulation events: coagulopathy, disseminated intravascular coagulation, thrombocytopenia or thrombocytosis
- Systemic inflammatory response related criteria: tachypnoea, hypopnoea, leucocytosis, leucopenia, hypothermia, hyperthermia, tachycardia and bradycardia

### **8.3 Recording Procedures**

Clinical investigators and ultimately the Principal Investigator (PI) have the primary responsibility for AE identification and documentation,

All adverse events and adverse device effects should be documented. Depending on the nature of the event the reporting procedures below should be followed. Any questions concerning adverse event reporting should be directed to the Principal Investigator in the first instance.

The investigator is responsible for reporting all (S)AEs occurring during the course of the study. AEs (serious or non-serious) observed by the investigator and/or reported by the subject must be recorded in the patient file and subsequently in the CRF, i.e. the period of time from the first (= signature of informed consent and/or the presumed will of the participant) to the last protocol-specific procedure (Visit 6 on Day 28 or date of death) regardless of the study product relation assessment.

All observed or volunteered adverse device events (serious or non-serious) and abnormal test findings, regardless of treatment group or suspected causal relationship to the investigational device or study treatment(s) will be recorded.

AEs or abnormal test findings felt to be associated with the study treatment(s) will be followed until the event (or its sequelae) or the abnormal test finding resolves or stabilizes at a level acceptable to the investigator.

All AEs, serious and non-serious, will be fully documented in the appropriate CRF. For each AE, the investigator will provide the onset, duration, intensity, treatment required, outcome and action taken with the investigational product.

For all AEs, sufficient information will be pursued and/or obtained so as to permit an adequate determination of the outcome of the event (i.e., whether the event should be classified as a SAE) and an assessment of the causal relationship between the AE and the investigational study treatment.

### **8.4 Assessment of Adverse Events**

After collecting information about an occurred event, the investigator assesses if it is a reportable event and has to be reported to the IEC and competent authority, respectively.

One of the following reporting criteria must be fulfilled:

- an SAE that could have been caused by an IMD or occurred in connection with a procedure carried out during the clinical trial.
- any investigational medical device deficiency that might have led to a SAE if
  - suitable action had not been taken or
  - intervention had not been made or
  - if circumstances had been less fortunate,
- new findings/updates in relation to already reported events.

## 8.5 Reporting of Reportable Events

The Sponsor-Investigator is responsible for reporting to the IEC and competent authority according to the following details.

- Provision of reportable events to the IEC and competent authority according to the following time frames: SAE which indicates an imminent risk of death, serious injury, or serious illness and that requires prompt remedial action for other patients/subjects, users or other persons or a new finding to it: **immediately**, but not later than **2 calendar days** after awareness by Sponsor-Investigator of a new reportable event or of new information in relation with an already reported event.
- Any other reportable event related to the medical device under investigation or due to study related procedures: **immediately**, but not later than **7 calendar days** following the date of awareness by the Sponsor-Investigator of the new reportable event or of new information in relation with an already reported event.
- Send a list of all reportable events and a safety report of the trial subjects on a yearly basis to the IEC and competent authority over the entire duration of the clinical trial.

The form "Clinical investigations of medical devices: Notification of serious adverse events concerning Switzerland" by Swissmedic is to be used.

